#### Aim 2: To establish whether a future trial of effectiveness is feasible

Data on the research process and participant compliance will be evaluated. The quantitative data on recruitment and retention of participants, completion of measures by each participant group (parents, child, teacher, observed) and adherence to the intervention protocol will be assessed relative to the relevant progression criteria described in table 2. These have been informed by existing school-based trials.^48 49^ As above, qualitative findings from the process evaluation and toolkit iteration feedback will be integrated to explain quantitative findings. Should all relevant progression criteria be rated ‘green’, a future trial of ef will be considered feasible. Should criteria be amber or red as the study progresses, potential mitigating modifications will be discussed, such as removing the requirement for parents to actively engage with the toolkit.

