Given that the aim of the study is not to assess effectiveness or efficacy, the potential for the intervention to change between participants, and the case-series design, this study will not be powered to conduct a conventional between-individuals analysis. Instead, we will use multiple individual measurement points to analyse within-individual change and assess whether this replicates (at a descriptive level) across individuals. The pragmatic choice of eight schools allows for this purposive sampling, and both the minimum and maximum sample size of children is sufficient to address our objectives. Based on the mean number of children in eligible year groups in Devon schools, and a conservative estimate of prevalence of ADHD in this age group of approximately 3%, it is expected that each school will have four to eight eligible children, of whom we hope to recruit at least 50%. The recruitment target is feasible: school staff have indicated that a toolkit for ADHD would be perceived as useful and not burdensome as they believe it would be beneficial to their wider classroom management (the planning group highlight the data collection burden as being the reason that teachers should only have one participating student per class).

An established set of study progression criteria are shown in table 2 and will be used to assess success in terms of meeting the study aims. Criteria relate to the recruitment of schools (five or more being acceptable), recruitment of parents and teachers, and completion of study measures as well as some basic metrics of fidelity. The criteria will be reviewed throughout the study, and where individual criteria are Amber or Red, a core academics team meeting and a planning group meeting will be held to discuss, agree and then implement modifications to the study procedure or content.

**Table 2 T2:** Study progression criteria

	Green: acceptable	Amber: discuss, modify	Red: redesign	Assessing
Recruitment of schools	6 or more	5	4 or fewer	Feasibility
Recruitment: teachers, children, parents (considered as separate groups)	>65%	20%–65%	<20%	Feasibility
Retention of schools, teachers, children and parents in study	>65%	40%–65%	<40%	Feasibility
Training completed (teachers)	>90%	70%–90%	<70%	Acceptability and feasibility
Introductory video watched (parents)	>50%	20%–50%	<20%	Acceptability
Child strengths activity completed	>50%	20%–50%	<20%	Acceptability
Adherence to digital Daily Report Card	>70%	50%–70%	<50%	Acceptability

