#### Adverse effects of intervention

It is possible that the intervention will lead to adverse effects or negative impacts on participating children, such as feeling singled out due to the intervention leading to social exclusion from the peer group.^32^ The study planning group will contribute to identifying potential adverse effects (*as of 21 March social exclusion is the most prominent concern*), and qualitative data will be collected from participants at the feedback and process evaluation stages to assess perceptions of negative impacts of the intervention. Modifications will be made as needed in relation to this through consultation with the planning group and the academic advisory team.

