### Analysis

#### Aim 1: To assess whether the toolkit is feasible and acceptable for schools to implement

We will use the definition of acceptability proposed by Sekhon *et al*^46^: ‘a multi-faceted construct that reflects the extent to which people delivering or receiving a healthcare intervention consider it to be appropriate, based on anticipated or experienced cognitive and emotional responses to the intervention’. Qualitative data from both the toolkit iteration interviews and the process evaluation interviews and focus groups will be audio recorded, transcribed and analysed using the Framework method and Thematic analysis.^47^ An initial coding framework will be developed after reading and re-reading transcripts. Deductive codes derived from the research questions and inductive codes within the data will be identified. This framework will be applied independently to three transcripts; discrepancies in coding will be discussed and revisions made to the framework which will then be applied to the remaining transcripts, with further discussion and revision where necessary.

Responses relating to each component of the toolkit will be synthesised in a framework in order to assess the acceptability of the evolving and final prototype; specifically to assess whether the components and the overall toolkit are considered appropriate to support children with ADHD in school. In addition, acceptability of the toolkit will be quantitatively assessed against the study progression criteria that relate to completion of each component of the toolkit, attendance at toolkit-related meetings, and the percentage of occasions the participant reports using the toolkit as instructed. The qualitative findings will be used to explain and further explore quantitative results in a mixed-methods synthesis. Modifications will be made iteratively as findings emerge, and by the end of the study each indicator should be in the ‘green’ range in order to indicate that the toolkit is acceptable.

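### The Aim 2 all-green rule contains no adverse-effect criterion, and the negative-impact data that the protocol collects are not linked to the feasibility verdict

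*Protocol article*

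**What the plan says.** The Sample size section makes the Table 2 progression criteria the yardstick for success against the study aims, and calls a team meeting and a planning group meeting whenever a criterion is amber or red.

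Aim 2 of the Analysis section states the decision rule. If every relevant criterion is green, "a future trial of ef will be considered feasible". (The cut-off word reads as a truncation of effectiveness and is not part of this point.) The role of the qualitative data there is that "qualitative findings from the process evaluation and toolkit iteration feedback will be integrated to explain quantitative findings".

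Aim 1 is worded differently. It begins with qualitative work on the prototype in its successive forms: "Responses relating to each component of the toolkit will be synthesised in a framework in order to assess the acceptability of the evolving and final". It then adds the progression criteria as a further, quantitative assessment, and says that "by the end of the study each indicator should be in the ‘green’ range in order to indicate that the toolkit is acceptable".

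The section on adverse effects acknowledges that "It is possible that the intervention will lead to adverse effects or negative impacts on participating children", gives being singled out and socially excluded as the leading example, and plans qualitative data on perceived negative impacts at the feedback and process-evaluation stages. The stated consequence is modification as needed, after consulting the planning group and the academic advisory team. Ethics and dissemination repeats the risk and the plan for feedback.

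**The concern.** The Aim 2 sentence is a sufficient condition: all green gives feasible. If no row can turn amber or red because of harm, the harm data cannot alter that verdict, and the meeting triggered by an amber or red rating is never called on account of harm. A toolkit with good recruitment, completion and adherence, but with children repeatedly reporting that they feel singled out, would pass Aim 2 as written.

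The verdict matters beyond logistics. The Design section ties being acceptable and feasible to suitability for further evaluation, first in a pilot and then in a definitive cluster randomised trial.

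**Working it through.** **1. Inputs.** Children: 8 schools × 2 = 16 and 8 × 4 = 32, which reproduces the 16–32 in the Sample size section. Retention row of Table 2 ("Retention of schools, teachers, children and parents in study"): green above 65%, amber 40%–65%, red below 40%.

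**2. Row-by-row reading of Table 2.** The 14 rows are:
- recruitment of schools; recruitment of teachers, children and parents; retention (3);
- teacher training, parent introductory video, child strengths activity, Daily Report Card adherence (4);
- completion of teacher, parent, child and observational measures (4);
- meeting attendance, use as instructed, completion of follow-up qualitative data (3).

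Total 3 + 4 + 4 + 3 = 14. Rows that count a negative impact: 0.

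**3. What retention can detect.** The smallest number retained, k, with k/n > 0.65:
- n = 32: 20/32 = 62.5% (amber), 21/32 = 65.6% (green), so 32 − 21 = 11 may leave (34%).
- n = 16: 10/16 = 62.5% (amber), 11/16 = 68.8% (green), so 16 − 11 = 5 may leave (31%).

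The row does not separate reasons for leaving, and an affected child who stays counts as retained.

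**4. How complete the child's own account need be.** The in-term feedback sessions are specified for school staff and parents; child interviews come in the follow-up period. The follow-up qualitative row is green above 50%, so 17 of 32 or 9 of 16 interviews suffice, and 15 of 32 or 7 of 16 children could go uninterviewed with the row green.

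**5. Illustration only.** The protocol gives no harm rate. At assumed rates of 10%, 25% and 50%, the expected number affected is 1.6, 4 and 8 of 16 children, or 3.2, 8 and 16 of 32. If those children stay and the completion and adherence targets are met, no row need change colour.

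**6. The rules side by side.**

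| Place | Quantitative condition | Role of qualitative findings |
|---|---|---|
| Aim 1, acceptability | indicators should be green | assess acceptability directly |
| Aim 2, feasibility of a trial | all relevant criteria green | explain the quantitative results |
| Subaim A, outcome measures | completion green | a second condition: no major barriers to repeated completion |

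A questionnaire thus has to pass a qualitative test as well as a numerical one. The trial-feasibility verdict does not.

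**The case against.** The strongest reply is that harm has its own route. The planning group helps to identify adverse effects, negative impacts are sought during use and at follow-up, and changes are made with the planning group and advisory team and recorded in a change log. The toolkit can be refined within a term if major issues arise. The patient and public involvement section has the planning group consulted on whether a trial is feasible, and the ethics section covers withdrawal and the child's best interests. It also refers to further risk mitigation in a supplement that is not at hand. All of this stands. None of it, in the text available, gives a harm finding any stated power over an all-green result.

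A reader might infer that all-green also declares the toolkit acceptable regardless of harm. The protocol does not support that. Aim 1 defines acceptability to include emotional responses, assesses it through a qualitative synthesis, and words all-green as something to be reached, not as the whole test. Recurrent reports of exclusion would fall within that assessment.

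A reader might also infer that all-green sends the toolkit straight to a definitive trial. The Design section puts a pilot first, and no passage makes progression automatic.

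Finally, the retention figures test one row. If 11 of 32 children left early, Daily Report Card adherence (green above 70%) and use as instructed (green above 75%) could fall to about 21/32 = 66% on an all-enrolled denominator, which is amber. That denominator is not stated, and late leavers would move these rows less. So the figures show what the retention row tolerates, not that every row would stay green.

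**Conclusion.** The point holds for Aim 2. The feasibility rule is sufficient on Table 2 alone, 0 of 14 rows address adverse effects, and the negative-impact data are not connected to the verdict. The only indirect signal, retention, stays green with up to 11 of 32 (34%) or 5 of 16 (31%) children leaving for any reason, and it misses affected children who remain. Aim 1 is partly protected by its qualitative synthesis, but does not say that unresolved harm bars a conclusion of acceptability.

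This rests on reading the Aim 2 sentence literally and on 16 to 32 children enrolled. It makes no prediction that harm will occur. Because partial safeguards exist, this is a decision rule that should be tightened, not a flaw that undermines the study.

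**What to change.** Rewrite the Aim 2 rule in the two-part form of Subaim A. A future trial is considered feasible if all relevant progression criteria are green and the qualitative findings (feedback sessions, process evaluation, stated reasons for withdrawal) show no unresolved negative impact attributed to the toolkit. The planning group and the academic advisory team would judge what is unresolved, using the change log. State the same condition under Aim 1, and report toolkit-related withdrawals separately from other attrition.

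The condition should not depend on showing that an impact does not recur under a later version. The last school has no later version, so one report there could never be cleared.

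Cost: a sentence under each aim and one reporting line, using data, groups and a log already planned. The downside is that feasibility becomes slightly harder to conclude and the verdict includes a judgement as well as counts.

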##### Subaim A

In order to identify suitable outcome measures to assess core ADHD symptoms, child and teacher well-being and an appropriate primary outcome for a future definitive trial, the acceptability and feasibility of using the individual measures will be evaluated following the steps above and in relation to the threshold set in the progression criteria. Measures will be considered suitable if there is a high level of compliance with completion (ie, each meet the green criteria), and qualitative findings indicate no major barriers to completing the measure on repeated occasions. Should measures be identified as unsuitable between toolkit iterations, new measures will be identified with the planning group and the data collection plan modified. For example, if the ADHD symptoms measure is too burdensome to complete as frequently as required, other briefer ADHD symptom scales will be explored, or the data collection frequency may be modified. The two versions of the CHU9D will be compared to assess whether child-report is sufficient. To *identify an appropriate primary outcome for a future trial*, participants’ qualitative responses to direct questions regarding what they think the most important outcome should be (and why), collected during the process evaluation, will be synthesised. Findings will be discussed with the planning group and advisory team prior to deciding on the final primary outcome measure.

##### Subaim B

In order to test a framework for costing the toolkit, and for assessing cost-effectiveness in a future definitive trial, the detailed information collected from the draft framework will be assessed following baseline data collection, and modifications made to the framework where free-text responses indicate additional resources not captured in the draft framework. The process evaluation interviews and focus group data will also contribute to understanding changes in resource use, which will be aligned with the follow-up responses regarding resource use in order to ascertain whether the framework is adequate and sensitive to changes in resource use.

The data captured on a bespoke form relating to the costs of setting up and delivering the toolkit will be assessed to expand the framework for accurately costing the toolkit’s delivery and potential savings, and the costs of delivering the prototype intervention will be calculated (including costs for staff time, training and delivery of components). This framework will be revised in line with study findings with the aid of health economists, with a final framework developed by the end of the study that would allow for cost-effectiveness to be formally assessed in a future definitive trial.

##### Subaim C

Assess whether measures of behaviour, classroom functioning and teacher-reported ADHD symptoms indicate improvement following use of the toolkit. *To explore whether there is indication that the toolkit may be efficacious*, quantitative data will be visually analysed within schools and participants, describing the nature of change over time and in relation to the intervention, following recommendations.^31^ Non-parametric analysis of the data will be considered, for example, by calculating Tau-U statistics. As the toolkit will be refined between schools participating, it would be irrelevant to compare measures across individuals who received different iterations of the toolkit; the focus will therefore be on assessing whether there is initial indication of improvement in outcomes, and whether any effect is replicated across individuals. Comparisons between the magnitude of change seen between those who receive earlier and later iterations of the toolkit will be carried out as it is anticipated that later iterations, modified to be more acceptable and feasible, would result in greater evidence of behaviour change. This will be an exploratory analysis. The core and target behaviours chosen across study participants will also be explored in a descriptive manner in order to assess the use of the behaviour web, targets and modules.

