**Ethics and dissemination:**

Ethical approval has been obtained. Results will be presented in journal articles, conferences and through varied forms of media to reach policymakers, stakeholders and the public.

Strengths and limitations of this studyThis study uses an iterative staggered design in order to refine an intervention throughout the research process.Measures of acceptability and feasibility of the intervention and of the ability to evaluate it in a rigorous trial setting will be reviewed against continuation criteria throughout the study.Multiple informants will provide relevant data, including school staff and parents, and data on both positive and adverse outcomes will be captured.However, the iterative nature of the study means that different participants will not receive the same intervention, therefore group-level effects cannot be delineated.Alternate analyses will be used to ascertain whether there are patterns of change in symptoms and functioning that replicate across individuals instead.

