## Methods and analysis

### Design

A randomised iterative mixed-methods case-series design will be used. Schools will be the units of randomisation, and will be randomised to the time (school term) when they will use the toolkit. The toolkit will be refined after each school has used it for one term, or more frequently if major issues are highlighted during a school’s use of the toolkit. Small, theory-based and data-driven changes hypothesised to be relevant across the school context will be made, as well as reactive changes addressing barriers to implementation. Randomisation to using the toolkit in different school terms allows for inferences to be made as to whether the intervention is improving outcomes, with consistent improvement following the introduction of the core components enabling researchers to potentially rule out alternative explanations for behaviour change, such as improvement due to other support in place or differences in behaviour across the school year. If baseline symptoms and functioning remain on stable trajectories for children across schools, changing only when the intervention is introduced, this implies it is the intervention rather than an alternate factor stimulating the change. It is a commonly used design for single-subject analyses where the intervention cannot be withdrawn and re-implemented such as in an ABAB design.^25–27^

Eight schools will participate in total in two recruitment cohorts of four (in order to avoid later participating schools having to sign up to the study years in advance); each cohort will enter the study at a different time. Schools in each cohort will then be randomly assigned their individual baseline term in the study using a computerised random sequence generator (see figure 1). The length of the baseline period will be the same for each school (one school term), with schools within each cohort entering their baseline period in different school terms; the term in which the intervention is delivered is therefore staggered across the study (figure 1). This design will allow for refining and adapting the toolkit and its implementation based on ongoing participant feedback, maximising the chances it has of being acceptable and feasible (and therefore suitable for further evaluation in a pilot and then definitive cluster randomised controlled trial) by the end of the study.

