### Sample size

The planning group has advised that to minimise burden of data collection on teachers, each class teacher should have a maximum of one child participant however this may be revised during the course of the study; for example, if a school feels strongly that several children in one class may benefit, or if two eligible children in the same class also have TA support and the teacher wishes both to participate. Estimating that each of the eight participating schools will have 2–4 participating children and teachers, there will be a total of 16–32 child participants, 16–64 parents, and 16–64 teachers and TAs along with eight SENCos. The total sample size will depend on the distribution of participating parents, teachers and TAs and the distribution of eligible children across different classes within schools: table 1 indicates the minimum and maximum sample sizes.

**Table 1 T1:** Sample size minimum and maximum

Participant type	Minimum number	Maximum number*
School	6	8
Children	16	32
Parents or carers	16	64 (ie, 2 parents per child)
SENCos	8	8
Teachers	16	32
TAs	0	32

*Maximum number based on every eligible school recruiting four pupils, each of which have a different class teacher. We anticipate actual numbers of TAs will be lower than the maximum.

SENCo, special educational needs (and disabilities) coordinator; TA, teaching assistant.

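### Subaim C judges replication of benefit across individual children, although the toolkit is introduced and refined by school, so 16–32 children supply at most 8 separately timed phase changes

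*Protocol article*

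**What the plan says.** All locations are in the protocol article.

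- **Unit that receives the timing (Design):** "Schools will be the units of randomisation, and will be randomised to the time (school term) when they will use the toolkit". Each school has one baseline term, of equal length in every school, followed by one intervention term. Schools within a cohort start in different terms.
- **Unit at which the toolkit changes (Design):** "The toolkit will be refined after each school has used it for one term, or more frequently if major issues are highlighted".
- **Where the inference comes from (Design):** if children's trajectories are stable across schools and shift only when the toolkit arrives, other explanations, such as other support or changes over the school year, become less likely.
- **Numbers (Sample size):** "Estimating that each of the eight participating schools will have 2–4 participating children and teachers, there will be a total of 16–32 child participants".
- **Unit of replication:** Subaim C asks "whether there is initial indication of improvement in outcomes, and whether any effect is replicated across individuals". The Sample size section plans to "analyse within-individual change and assess whether this replicates (at a descriptive level) across individuals". The strengths and limitations list speaks of "patterns of change in symptoms and functioning that replicate across individuals instead".

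Subaim C also has the data inspected visually at both school and participant level. It regards comparison between individuals on different iterations as beside the point, but then plans an exploratory comparison of earlier with later iterations. Nothing in the article requires an effect to recur across schools, or treats the children of one school as a single replicate.

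**The concern.** In a staggered case series, a replication is persuasive because a second unit changes at a different, independently assigned time. Here that unit is the school. A second child in the same school adds information about how individuals respond, but it does not add a second introduction time. A new behaviour policy, a staffing change or a difficult term would touch all participating children in the school at the moment the toolkit arrives. With individuals as the unit, that single event can be reported as two to four replications.

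The view that comparison across iterations is beside the point sharpens this. Since versions normally change between schools, the children left as same-version replicates are mainly those of one school, where a school or term event cannot be separated from a toolkit effect.

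At stake is the credibility of the early-utility message. It could appear to rest on as many as 32 confirmations when the design can offer no more than 8.

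**Working it through.** **Reproducing the plan's figure.** 8 schools × 2 children = 16, and 8 × 4 = 32. The stated range of 16–32 children is reproduced. The number of separately timed introductions is at most 8, one per school. If only the Table 1 minimum of 6 schools takes part, it is at most 6.

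**What same-school children share.**

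| Feature | Level at which it is set | Source |
|---|---|---|
| Start term | School | Design |
| Scheduled phase change | School (one baseline term, then one intervention term) | Design; Table 3 |
| Toolkit version | School, unless changed during the term | Design |
| Coordinator | School (8 SENCos for 8 schools) | Table 1; Intervention delivery |
| Modules and targets | Child | Intervention delivery; Table 3 |
| Rater | Usually child (one per class teacher, may be revised) | Sample size |

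**Illustration 1: effective number of replicates.** With m children per school and within-school correlation ρ of the baseline-to-intervention change, the effective number is 8m / [1 + (m − 1)ρ]. The protocol gives no ρ, so the values are assumptions.

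| ρ (assumed) | m = 2 (16 children) | m = 4 (32 children) |
|---|---|---|
| 0.1 | 16/1.1 = 14.5 | 32/1.3 = 24.6 |
| 0.3 | 16/1.3 = 12.3 | 32/1.9 = 16.8 |
| 0.5 | 16/1.5 = 10.7 | 32/2.5 = 12.8 |
| 1.0 | 16/2 = 8 | 32/4 = 8 |

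The loss is small at low correlation with two children per school, and large at high correlation with four.

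**Illustration 2: one event read several times.** Assume no toolkit effect. In each school, independently and with probability q, a school-wide change coincides with introduction and moves every child there; no other child improves. Suppose a reader takes three improvements as replication. Both q and the threshold of three are assumptions.

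- Four children per school: three or more children improve whenever at least one school is hit, so the probability is 1 − (1 − q)^8.
- Two children per school: at least two schools must be hit, so it is 1 − (1 − q)^8 − 8q(1 − q)^7.
- Counting schools: at least three of 8 must be hit (binomial tail).

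| q (assumed) | Children, m = 4 | Children, m = 2 | Schools |
|---|---|---|---|
| 0.05 | 0.34 | 0.06 | 0.006 |
| 0.10 | 0.57 | 0.19 | 0.04 |
| 0.20 | 0.83 | 0.50 | 0.20 |

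With four children per school, a single affected school is enough. The last column is not zero, so counting schools removes the multiple reading of one event but does not make a low threshold safe.

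**The case against.** The strongest reply is that there is no counting rule to inflate. The Sample size section says only that the study will "assess whether this replicates (at a descriptive level) across individuals". The method is visual, and the article states no test, significance level or required number. It never calls the children independent. School-level reasoning is already present in the Design section and in the school-level plots of Subaim C. Exposure is not identical within a school either: modules and targets differ by child, SENCos have latitude over duration and dose, the toolkit may be altered mid-term, and different teachers normally rate different children. Operational criteria may also sit in a fuller plan that is not shown.

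Much of this stands. It lowers the likely within-school correlation and rules out any claim about an actual error rate. It does not answer the mismatch: the unit of replication is named three times, each time as the individual, while the inferential argument runs across schools. Plotting by school governs display and leaves the replication criterion unchanged. Separate raters do not remove a shared term, coordinator or school event.

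A reader might infer more than the document supports:

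- **That an inflated signal would carry the study into a trial.** Aim 2 ties trial feasibility to the Table 2 criteria on recruitment, retention, completion and adherence. None is an efficacy outcome.
- **That a false-positive rate can be stated.** One can invent a rule such as 22 or more of 32 children improving (2.5% under independence) and obtain 3.7% at an assumed correlation of 0.1 and 8.6% at 0.5. Both the cut-off and the correlation would be the reader's own. At 0.1 the result hardly differs from the 3.5% (9/256) for 7 or more of 8 schools.
- **That Tau-U p-values would mislead.** Tau-U is only mentioned as a possibility, and no p-value is planned.

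**Conclusion.** The concern holds as a mismatch between the unit that carries the design's inference (the school) and the unit by which Subaim C judges replication (the child). Its firm size is structural: at most 8 separately timed phase changes stand behind 16–32 children, and one event in one school can appear as up to four replications. That rests on the stated school-level timing, on 2–4 children per school, and on same-school children normally receiving the same version. The tabulated probabilities and effective numbers rest on assumed correlations, event probabilities and thresholds, and show direction and order of magnitude only.

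The consequence is limited to a secondary, exploratory and descriptive conclusion. It does not follow that the study is invalid, that the progression decision is affected, or that the protection from randomised timing is lost; the Design section still provides it, and Subaim C only needs to use it. The wording is worth correcting before analysis.

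**What to change.** In Subaim C, and to match in the Sample size section and the strengths and limitations list:

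1. State that replication is judged across schools, using their staggered start terms.
2. Keep the individual plots, grouped in one panel per school, and count each school as one replicate.
3. Report how many schools, in order of toolkit iteration, show improvement at introduction, and describe the variation between children within each school.
4. Do not describe same-school children as independent replications.

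A fixed cut-off such as 7 of 8 schools is not needed and would sit badly with this design. Subaim C expects later iterations to do better, so a toolkit that failed in two early schools and was then successfully refined would be labelled as not replicated. Reporting schools in iteration order lets that pattern show.

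The cost is a few sentences, with no new data. The drawback is that the reported number of replicates falls from 16–32 to at most 8, which looks less favourable but matches what the staggered introduction can support.
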